### Statistical analysis

Continuous variables will be described as the mean (with standard deviation [SD]) or median (with interquartile range [IQR]) depending on whether they fit a normal distribution. Categorical variables will be described as counts and percentages. Comparisons between groups will be performed using appropriate statistical tests (*chi-square* test for categorical variables; Student’s *t* test or Mann^‒^ Whitney *U* test for continuous variables). To address the potential confounding variable introduced by preference-based group allocation, we will implement propensity score methods, including propensity score matching (PSM) and inverse probability of treatment weighting (IPTW).^[30]^ Multivariate analyses for covariate correction will be conducted using logistic regression, linear regression, and Cox proportional hazards regression, depending on the type of outcome variables. Variance inflation factors (VIFs) will be assessed *via* correlation matrices, with variables with a VIF < 3.0 retained. Firth’s penalized maximum likelihood bias reduction method for Cox regression will be implemented to handle the monotone likelihood. All analyses will be performed using R (version later than 4.4.0), and a two-tailed p value of < 0.05 will be considered to indicate statistical significance. Detailed methodologies for outcome analysis, subgroup evaluation, and sample size estimation are provided in Supplementary materials 3–4.

## Discussion

Currently, the use of MRD for monitoring postoperative recurrence of lung cancer requires a high level of accuracy, and high-quality evidence supporting the predictive value of MRD in adjuvant therapy is lacking. Postoperative chemotherapy, long-term targeted therapy, and immune checkpoint inhibitor treatments impose certain toxic side effects and financial burdens on patients. Therefore, first, this study primarily aims to develop a recurrence monitoring method that integrates multiomics data to improve sensitivity. Additionally, this is the first prospective, interventional, multicenter real-world study to explore the rationale of MRD-guided postoperative management for patients with resectable NSCLC.

Although this study adopts a preference-based allocation design, all participants will be enrolled under strict inclusion and exclusion criteria, ensuring a clinically homogeneous study population. This approach reflects real-world clinical practice where patient preference influences treatment choice. To minimize potential selection bias, we will collect detailed baseline variables and apply propensity score methods to adjust for measurable confounders. Additionally, we will perform multivariate analyses for covariate correction. Subgroup analysis will also control for baseline imbalances. Although this design may not support strict causal inference, it allows for a more pragmatic evaluation of MRD-guided management strategies in real-world clinical practice.

Studies have shown that MRD can be detected by liquid biopsies well before recurrence can be detected by standard clinical methods.^[31,32]^ Moreover, both plasma metabolomics^[33]^ and proteomics demonstrate strong correlations with cancer risk. With respect to radiomics, studies have reported that integrating radiological features with ctDNA detectability improves the prediction of NSCLC outcomes.^[34, 35]^ Multiomics integration has been used in early tumor detection and has shown high accuracy.^[36, 37]^ Therefore, our study pioneers the integration of plasma multiomics, radiomics, and clinicopathological features, which is crucial for increasing the sensitivity and accuracy of noninvasive monitoring methods for postoperative lung cancer recurrence.

Previous studies have revealed the immense potential of MRD in guiding postoperative adjuvant therapy. In the FLAURA2 study,^[38]^ for patients who were ctDNA positive at baseline, the addition of chemotherapy to standard osimertinib treatment further prolonged progression-free survival (PFS). However, for ctDNA-negative patients at baseline, combining chemotherapy did not provide an additional improvement in PFS. Another study^[39]^ revealed that compared with patients who were ctDNA-positive at either time point, NSCLC patients who were ctDNA-negative at both the neoadjuvant and postsurgical time points had significantly higher 18-month event-free survival rates, suggesting that combined MRD testing could help identify patients who may have been cured and thus who do not require additional adjuvant therapy. Nevertheless, these findings remain confined to exploratory analyses derived from observational studies, serving solely to hypothesize the therapeutic guidance value of ctDNA-MRD. In contrast, this study will systematically investigate the clinical feasibility, safety, and efficacy of MRD-guided adaptive strategies through comparative analysis with standard postoperative management. With respect to the reason for choosing 3–6 months as the MRD monitoring time, we considered clinical safety and feasibility. The European Society of Medical Oncology (ESMO) recommends the use of ctDNA assays for tumor patients ^[40]^ and reported that tumor-informed ctDNA detection generally progresses from ctDNA detection to clinical relapse in < 6 months. A TRACERx study ^[15]^ also verified that ctDNA surveillance every 3–6 months identified impending disease relapse in an additional 20% of patients whose ctDNA had been negative within 120 days after surgery. These findings demonstrated the value of this detection interval for early warning of recurrence. Moreover, longitudinal detection in prospective studies or randomized controlled trials of ctDNA-based MRD detection in resectable tumors occurred mostly 3–6 months after surgery, which may also be consistent with the follow-up time.^[41]^ However, whether this timepoint is the most appropriate needs further validation. The evaluation endpoints are formulated in accordance with the ESMO to define whether an intervention is clinically meaningful as a > 5% improvement in survival or an improvement in DFS with an HR < 0.65 (lower limit of the 95% confidence interval) for studies without mature survival data. Noninferior OS or DFS with reduced treatment toxicity or improved QoL can also be clinically meaningful.^[42]^

This study will help clarify the therapeutic value of MRD-guided postoperative management in lung cancer patients. If MRD-guided strategies result in superior patient outcomes, they could significantly alter clinical decision-making. If no significant difference in patient prognosis is observed but a notable reduction in adverse effects or treatment costs is achieved, incorporating MRD into clinical practice could still serve as a viable alternative, effectively ensuring timely intervention for high-risk subgroups while sparing patients from unnecessary therapy toxicity and thereby harmonizing survival benefits with quality-of-life preservation. From a broader perspective, this study exemplifies the convergence of translational medicine and artificial intelligence, providing a blueprint for real-world validation of liquid biopsy technologies. Elucidating the interplay between residual tumor biology and host responses advances our mechanistic understanding of cancer recurrence. The establishment of a nationwide NSCLC postoperative database and digital platform further facilitates future biomarker discovery and precision oncology research.

In summary, this study represents a transformative endeavour for redefining the postoperative management of early-stage NSCLC by bridging cutting-edge multiomics technologies with real-world clinical practice. The integration of plasma metabolomics, proteomics, radiomics, and ctDNA-based MRD monitoring will establish a novel paradigm for noninvasive recurrence surveillance and address the sensitivity limitations of current imaging-centric approaches. On the other hand, by pioneering a ctDNA-guided adaptive therapeutic strategy, this study will challenge the conventional “one-size-fits-all” adjuvant therapy modality and offer a customized framework to tailor interventions based on MRD dynamics, further contributing to the shift in global oncology practice from population-based guidelines to individualized biomarker-driven care.

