## Abstract

**Background and Objectives:**

Circulating tumor DNA (ctDNA)-based molecular residual disease (MRD) has been confirmed to predict postoperative recurrence of early-stage non-small-cell lung cancer (NSCLC), outperforming conventional imaging modalities by improving diagnostic efficiency and eliminating radiation-related risks. Integrating ctDNA with other liquid biopsy omics methods might further increase monitoring accuracy. In addition, patients with longitudinal undetectable MRD exhibit a favorable outcome and may be overtreated after radical surgery, while those traditionally not recommended for adjuvant treatment but with positive MRD may have not received appropriate disease management. This prospective real-world trial involving ten clinical centers across China aims to develop a multiomics noninvasive platform for recurrence prediction and to determine whether postoperative management guided by ctDNA is noninferior to standard care.

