## Interventional substudy: MRD-based adaptive postoperative management for lung cancer

### Settings

This prospective multicenter real-world study aims to evaluate whether compared with standard management, ctDNA-MRD-guided postoperative surveillance and adjuvant therapy strategies improve clinical outcomes and cost-utility in patients with stage IA-IIIA NSCLC. We will prospectively enroll 756 patients across 10 clinical centers. Participants will undergo real-world preference allocation to either the standard treatment group or the ctDNA-MRD-guided treatment group, with longitudinal monitoring at 3–6-month intervals. The primary endpoint is the two-year DFS rate (Figure 2).

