### Outcomes

The primary endpoint of this clinical trial is the two-year DFS rate after surgery, defined as the interval from the surgical date to objectively confirmed disease recurrence or death from any cause.

Secondary outcomes of interest include (1) overall survival (OS), (2) total treatment cost 24 months after surgery, (3) incremental cost effectiveness ratio (ICER), (4) sensitivity of the novel recurrence prediction model developed in the observational substudy, (5) timely diagnosis of recurrence in the new follow-up model developed by the observational substudy, and (6) ctDNA characterization during neoadjuvant/adjuvant therapy and its associations with clinical outcomes, including short-term efficacy (radiological and pathological response) and long-term survival. Total treatment cost refers to the expense of lung cancer-related treatment for the patient during the research period, including the drug cost, follow-up treatment cost, drug management cost (consultation fee, antitumor drug allocation fee, intravenous infusion fee, nursing fee, *etc*.), cost of follow-up laboratory tests and imaging, and management cost of adverse reactions of grade 3 or greater, with an incidence rate of more than 5%.

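### The comparison is stated both as non-inferiority and as improvement, and the Discussion would let a non-significant difference in prognosis stand in for non-inferiority

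*Protocol article*

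**What the plan says.** All places are in the protocol article.

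- **Abstract, Background and Objectives.** The trial is "to determine whether postoperative management guided by ctDNA is noninferior to standard care".
- **Interventional substudy, Settings.** The same comparison with standard management asks whether "ctDNA-MRD-guided postoperative surveillance and adjuvant therapy strategies improve clinical outcomes and cost-utility in patients with stage IA-IIIA NSCLC".
- **Statistical analysis.** After the software statement comes a general convention: "a two-tailed p value of < 0.05 will be considered to indicate statistical significance". Outcome analysis and sample size are referred to Supplementary materials 3–4.
- **Discussion, on the choice of endpoints.** Citing ESMO, the article says: "Noninferior OS or DFS with reduced treatment toxicity or improved QoL can also be clinically meaningful".
- **Discussion, on implications.** The condition becomes "If no significant difference in patient prognosis is observed but a notable reduction in adverse effects or treatment costs is achieved", and in that case MRD guidance is described as a possible alternative for practice.
- **Outcomes.** The primary endpoint is the two-year DFS rate. "Secondary outcomes of interest include (1) overall survival (OS), (2) total treatment cost 24 months after surgery", followed by the incremental cost-effectiveness ratio and others. Adverse events are not named as an outcome, although treatment-related adverse events are recorded (Data collection).

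**The concern.** Non-inferiority, superiority and absence of a significant difference are three different claims, and the article uses all three for one comparison. The third is not a valid route to the first. A test that fails to reject equality says only that the data are compatible with no difference; they may be equally compatible with a loss that nobody would accept. The criterion also rewards imprecision, because the smaller the effective sample, the easier it is to satisfy.

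This matters here because one element of the guided strategy leaves out adjuvant therapy when MRD is undetected one month after surgery (Interventions, Experimental arm). The main risk to exclude is a loss of DFS. The additional condition in the Discussion, fewer adverse effects or lower costs, puts no limit on that loss.

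**Working it through.** **The article's own counts.** 609 + 147 = 756; 378 + 378 = 756; 756 + 160 = 916. They agree. The sample size of 756 cannot be re-derived, because control rate, margin or effect, power and dropout are not in the article. It also does not reveal which hypothesis was used, since both kinds of design can land near it:

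- Non-inferiority: DFS 80% in both groups, 10-point margin, one-sided 0.025, 90% power gives 337 per group. With 10% dropout, 337/0.9 rounds up to 375, or 750 in total.
- Superiority: 75% against 85%, two-sided 0.05, 90% power gives 335 per group. With 10% dropout, 335/0.9 rounds up to 373, or 746 in total.

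**How often a real loss would be non-significant.** Inputs: n = 378 per group (Figure 2 legend); two-sided 5% level (Statistical analysis); control 2-year DFS p and true loss d are assumptions; no dropout and no adjustment. With q = p − d,

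SE = √([p(1−p) + q(1−q)]/n), and P(non-significant) ≈ Φ(1.96 − d/SE).

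At p = 0.80:

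- d = 0.05: SE = √((0.16 + 0.1875)/378) = 0.0303; d/SE = 1.65; Φ(0.31) = 62%.
- d = 0.075: SE = √((0.16 + 0.1994)/378) = 0.0308; d/SE = 2.43; Φ(−0.47) = 32%.
- d = 0.10: SE = √((0.16 + 0.21)/378) = 0.0313; d/SE = 3.20; Φ(−1.24) = 11%.

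Across the assumed range of control DFS:

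| True loss | 70% | 75% | 80% | 85% | 90% |
|---|---|---|---|---|---|
| 5 points | 69% | 66% | 62% | 56% | 45% |
| 8 points | 36% | 32% | 27% | 20% | 11% |
| 10 points | 18% | 15% | 11% | 7% | 3% |

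**Effect of propensity methods.** An assumed design effect of 1.3 from weighting multiplies SE by √1.3 = 1.14. At p = 0.80 the figures for 5, 7.5 and 10 points become 70%, 43% and 20%. If matching kept an assumed 60% of patients (226 per group), losses of 5, 8 and 10 points would be non-significant 75%, 49% and 31% of the time.

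**What a non-significant result can hide.** At p = 0.80 an observed deficit of 5.99 points is still non-significant. Its 95% limit lies at 0.0599 + 1.96 × √((0.16 + 0.7401 × 0.2599)/378) = 0.1197, a loss of about 12 points.

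**Comparison with a margin rule.** If the true loss equals the margin, a two-sided 95% confidence limit set against that margin wrongly supports the strategy about 2.5% of the time.

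**Power of that rule with 378 per group.** With true DFS 80% in both groups, SE = √(2 × 0.16/378) = 0.0291 and power = Φ(margin/SE − 1.96):

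- 5-point margin: Φ(−0.24) = 40%
- 8-point margin: Φ(0.79) = 78.5%
- 10-point margin: Φ(1.48) = 93%

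For 80% power the totals before dropout would be 2010, 786 and 504. These margins are illustrations, not values from the article.

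**The case against.** The strongest reply is that the article is condensed. A reader might infer that the trial decides its primary endpoint by a two-tailed p below 0.05, or that it has no margin. The documents do not support either. The 0.05 sentence is a general convention for all analyses, it is compatible with a two-sided 95% confidence interval read against a margin, and Supplementary materials 3–4, not shown, may hold both margin and test. That part of the reply stands.

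It is also fair that the sentence on non-significance is conditional prose in the Discussion, not in Outcomes or Statistical analysis; that the ESMO benchmark given just before it is put correctly; that the article concedes the design may not support strict causal inference; and that the guided strategy intensifies as well as withholds treatment, so a net loss is a risk to exclude and not an expectation.

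A reader might further infer that the benefit side of the trade has no endpoint. That is wrong: total treatment cost and the incremental cost-effectiveness ratio are listed outcomes, and only the adverse-effect half lacks one. Whether quality of life or utilities are measured is a separate question, which the supplements may answer.

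What remains is enough. No supplement can turn a non-significant difference into non-inferiority, and none can make the abstract and the Settings section ask the same question. If a margin exists, the Discussion sentence contradicts it.

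**Conclusion.** The point holds as an inconsistency in the stated hypothesis together with an invalid reading of a null result. For 378 per group and an assumed control 2-year DFS of 80%, a true 5-point loss would be non-significant about 62% of the time (45% to 69% over the assumed control range of 90% to 70%), a 7.5-point loss about 32% and a 10-point loss about 11%, and more often once propensity methods reduce the effective sample. These are frequencies of non-significance. They should not be read as rates of wrong endorsement: the Discussion also asks for a reduction in adverse effects or costs, and it is not shown to be the operative rule. The direction of the error does not depend on the assumed rates; only its size does.

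**What to change.** 1. State one primary hypothesis, in the same words, in the abstract, in the Settings of the interventional substudy, in Statistical analysis and in the Discussion.
2. If it is non-inferiority, claim it only when the lower limit of the two-sided 95% confidence interval for the propensity-adjusted difference in 2-year DFS (guided minus standard) lies above minus the prespecified margin. Test superiority only after that.
3. In the Discussion, replace the condition of no significant difference with the condition that non-inferiority is shown, and say that a non-significant difference without it is inconclusive.
4. Because that passage relies on fewer adverse effects, name the treatment-related adverse events already collected as a secondary outcome. The cost side needs no addition.

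The cost is mainly wording and is best met before results are seen. Some results that would have been called favourable become inconclusive. If 378 per group gives low non-inferiority power at the chosen margin, as it would at 5 points under the assumptions above, that power should be stated.
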